# Economic Burden to Subjects

# Consent Process

# Process to Document Consent in Writing

# Setting

# Resources Available

# *Multi-Site Research – N/A*

# ****Protected Health Information Recording****

# References

# Study Summary

| **Study Title** | “Effectiveness of adding a novel digital storybook intervention platform in therapy to improve speech, language, and literacy outcomes in children with hearing loss” |
| --- | --- |
| **Study Design** | Prospective clinical trial |
| **Primary Objective** | Determine if in-person speech-language therapy (SLT) with a novel digital storybook intervention (Hear Me Read, HMR) improves **vocabulary, speech and language outcomes** in young children who are D/HH compared with in-person therapy alone. |
| **Secondary Objective(s)** | Determine if in-person speech-language therapy (SLT) with a novel digital storybook intervention (Hear Me Read, HMR) improves **literacy outcomes** in young children who are D/HH compared with in-person therapy alone. |
| **Research Intervention(s)/ Investigational Agent(s)** | Hear Me Read! is an IOS-based software application that enables parents/caregivers and treating speech-language pathologists to partner together to help deaf/hard of hearing children (D/HH) achieve reading, speech and language goals through interactive digital storybook reading |
| **IND/IDE #** | N/A |
| **Study Population** | Children seen in the Hearing Program at Nationwide Children’s Hospital who are deaf/hard of hearing, their parent/caregiver, and their treating Speech Language Pathologist (SLP).  **Child Eligibility:**   - ***Inclusion:***   - Male and female children ages 3.0-5.11 years at time of initial assessment and:     - Bilateral Sensorineural or mixed hearing loss at least (PTA≥30dB) ***or***     - Auditory neuropathy in both ears - ***Exclusion:***   - English not primary language   - Standard score CLS >2 SD from normal on CELF-P3   **Parent/Caregiver Eligibility:**   - ***Inclusion:***   - Parent/caregiver of eligible child (must be child’s legal guardian) - ***Exclusion:***   - None   **Treating SLP Eligibility:**   - ***Inclusion:***   - Treating therapist/SLP for participating child - ***Exclusion:***   - None |
| **Sample Size** | Approximately 50 children and their parents/caregivers, and the child’s treating SLP. |
| **Study Duration for individual participants** | 1 year |

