# Study Endpoints

- 1. Describe the primary and secondary study endpoints.

The primary study endpoints acquiring the primary study outcomes of standardized behavioral measures of speech, language, and literacy outcomes. These include Raw Score, Standard Score, Percentile Rank, Age Equivalent, and Growth Scale Values where applicable for the following tests: Receptive One Word Picture Vocabulary Test, Clinical Evaluation of Language Fundamentals Preschool-3 and subtests). The clinical standard test-retest interval for these behavioral measures in D/HH children is 6 months.

Secondary outcomes include measures of the impact on therapy experience, book engagement/book-reading habits, and feedback on the design and usability of the Hear Me Read app. These will be measured with parent/caregiver and SLP questionnaires, and in-app metrics of app usage.

Primary outcomes are measured pre-trial, at 6 months (after 1st intervention arm), and at 12 months (after 2nd intervention arm). Secondary outcomes are measured at 6 months (after 1st intervention arm), and at 12 months (after 2nd intervention arm). Study phase will end upon cessation of data collection after the 2nd intervention arm and participants’ participation.

The secondary endpoint will be the completion of data analysis, which concludes the management of PHI.

- 1. Describe any primary or secondary safety endpoints.

N/A, as this study poses no more than minimal risk to patients enrolled.

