**Hear Me Read Training documents:**

- Hear Me Read – Treating Therapist Manual
- Hear Me Read – Parent/Caregiver User Manual

**Patient Medical and Demographic Information:** Obtained from the electronic medical record at NCH (see Section 27)

- - Records from Audiology, Speech-Language Therapy, ENT
  - General Demographics and PHI (see Section 27)
  - Audiologic measures
  - Speech perception
  - Degree of hearing loss
- Mode of communication (oral, total communication, manual/sign language)
- Etiology of hearing loss
- Technology (Hearing aid, cochlear implant, none) and dates of service
  - Maternal level education

6.5 What data will be collected during the study and how that data will be obtained.

Child participant data to be collected includes:

1. **Primary Outcomes:**

- Behavioral measures include age-appropriate behavioral surveys administered by a SLP to assess a child’s language and communication skills, conducted as part of standard clinical care. These consist of verbal or pointing tasks in response to verbal or picture prompts and questions. These are documented in **Therapist - Data collection Form** containing data **Pre-Trial SLP Evaluation, Post- SLT only SLP Evaluation, and Post-SLT+Digital SLP Evaluation** consisting of **(see Figure 1):**
  - Raw Score, Standard Score, Percentile Rank, Age Equivalent, and Growth Scale Values where applicable for the following tests.
    - **Speech and Language Outcomes**
      - Vocabulary
      - [Receptive One Word Picture Vocabulary Test (ROWPVT-4)](https://www.pearsonassessments.com/store/usassessments/en/Store/Professional-Assessments/Speech-%26-Language/Receptive-and-Expressive-One-Word-Picture-Vocabulary-Tests-%7C-Fourth-Edition/p/100000338.html#:~:text=The%20ROWPVT%2D4%20tests%20an,when%20presented%20with%20color%20illustrations.) (ages 2.0-70+), 10-15 min
      - Language
        - [Clinical Evaluation of Language Fundamentals Preschool-3 (CELF P3)](https://www.pearsonassessments.com/store/usassessments/en/Store/Professional-Assessments/Developmental-Early-Childhood/Clinical-Evaluation-of-Language-Fundamentals-Preschool-3/p/100002031.html?tab=product-details) (ages 3.0-6.11), 15-20 min

Subtests:

Word Structure (WS)

Sentence Comprehension (SC)

Expressive Vocabulary (EV)

Following Directions (FD)

Recalling Sentences (RS)

Basic Concepts (BC)

Word Classes (WC)

Indices (composite scores of selected subtests):

CLS (Core Language Score) (Ages 3-6)

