# Local Number of Subjects

12.1 Indicate the total number of subjects to be accrued locally.

A **power analysis** was performed, based off of Raw Scores with the following rationale: A repeated measures design will evaluate the effect of the intervention within person. In this case, the primary goal of the study is to compare the change across time during SLT therapy alone to the change across time with SLT + Digital. A sample size of 43 achieves 90% power to detect a mean of paired differences of 0.75 with an estimated standard deviation of 1.0 and with a significance level of 0.001 using a two-sided paired t-test.   We plan to enroll 50 children at NCH, as well as a parent/caregiver for each child and the child’s treating SLP.

12.2 If applicable, distinguish between the number of subjects who are expected to be enrolled and screened, and the number of subjects needed to complete the research procedures (i.e., numbers of subjects excluding screen failures.)

We expect approximately 411 unique D/HH children in the age range to be seen by our Hearing Program in 1 year, based on 2019 data. Of these, 141 completed a speech and language evaluation in that year and 270 did not. With prospective attention to scheduling and these volumes, we anticipate screening approximately 250-300 patients to achieve 50 that would enroll.

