# Data Management* and Confidentiality

17.1 Describe the data analysis plan, including any statistical procedures or power analysis.

Raw Score, Standard Score, Percentile Rank, Age Equivalent, and Growth Scale Values for the assessment tests will be measured. Power analysis was based off of Raw Score. A 2-by-2 repeated measures design consists of two groups of subjects, each measured at two time points. In this case, the primary goal of the study is to compare the change across time in group 1 to the change across time in group 2. Sample sizes of 13 in group 1 and 13 in group 2 achieve 92% power to detect a difference in mean changes of 2.0 with a standard deviation of 1.0 at the first time point, a standard deviation of 1.0 at the second time point, and a correlation between measurement pairs of 0.300. The significance level (alpha) is 0.010 using a two-sided, two-sample t-test. To detect a mean 1.5 point difference (all else being equal), we would need **21 patients in each group**. To detect a mean 1 point difference (all else being equal), we calculate we would need 44 patients in each arm.

We plan to analyze Intervention Period 1 (SLT) and Intervention Period 2 (SLT+Digital) together using mixed-effects models to account for differences between interventions 1 and 2. For the primary outcomes, evaluate baseline assessments and compare values between groups using Pearson chi-square tests, t-tests, and Wilcoxon-Mann-Whitney tests. If any imbalance in patient characteristics (e.g. age, frequency of therapy) is detected between groups, the imbalanced characteristics will be adjusted for in multivariable mixed-effects linear regression analyses.

All statistical analyses will be conducted using SAS Enterprise Guide, version 7.15 (SAS Institute Inc). Outcomes are reported for the intention-to-treat population and the also reported for the per protocol population. A 2-sided P < .05 was considered statistically significant.

17.2 Describe the steps that will be taken to secure the data (e.g., training, authorization of access, password protection, encryption, physical controls, certificates of confidentiality, and separation of identifiers and data) during storage, use, and transmission.

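### The protocol sizes the trial at alpha 0.001 and at 0.010 but decides at P < .05, with 14 scores all called primary, so the chance of a false positive on some primary score is well above 5%

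*Protocol*

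**What the plan says.** Section 12.1 bases the sample size on raw scores and a within-child comparison: "A sample size of 43 achieves 90% power to detect a mean of paired differences of 0.75 with an estimated standard deviation of 1.0", "with a significance level of 0.001 using a two-sided paired t-test". Planned enrolment is 50 children.

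Section 17.1 gives a second calculation, for two groups of 13 and a difference in mean changes of 2.0: "The significance level (alpha) is 0.010 using a two-sided, two-sample t-test". The same section closes with the rule for the analysis: "A 2-sided P < .05 was considered statistically significant". Nothing in the protocol ties 0.001 or 0.010 to the final tests.

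On outcomes, Section 4 states: "The primary study endpoints acquiring the primary study outcomes of standardized behavioral measures of speech, language, and literacy outcomes". Section 6.5 lists the scores under Primary Outcomes and asks for "Raw Score, Standard Score, Percentile Rank, Age Equivalent, and Growth Scale Values where applicable for the following tests". Raw score is singled out only as the basis for power, and no test or subtest is named there. The Study Summary gives as a secondary objective whether the intervention "improves literacy outcomes in young children who are D/HH compared with in-person therapy alone", yet the literacy scores sit under Primary Outcomes in Section 6.5.

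**The concern.** Two things are unsettled: which significance level decides the trial, and which result it is applied to. A primary score with p = 0.02 is significant under the rule in Section 17.1 and not significant at either level used for sizing. The strict sizing levels suggest an error control that the decision rule does not provide.

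Because every score carries the primary label and none leads, a significant result on any of them could be offered as support for the main hypothesis. For the three literacy scores it is not even fixed whether they may support a primary claim. If these choices are made after the results are seen, the reported P value will not mean what it appears to mean.

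**Working it through.** **1. Do the sizing levels reproduce?**

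Paired t-test (Section 12.1): n = 43, difference 0.75, SD 1.0, two-sided alpha 0.001. The noncentrality is √43 × 0.75 / 1.0 = 4.92 on 42 degrees of freedom. Noncentral-t power is 90.4%, and 43 is the smallest n that reaches 90%. This agrees with the protocol.

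Two-sample t-test on change scores (Section 17.1): SD 1.0 at each time and correlation 0.3, so the SD of change is √(1 + 1 − 2 × 0.3) = √1.4 = 1.183. With 13 per group, difference 2.0 and alpha 0.010, power is 92.4% against the stated 92%. The section's other two cases, 21 per group for 1.5 and 44 per group for 1.0, give 91.3% and 90.5%.

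So 0.001 and 0.010 are the levels actually used. At 0.05 the paired design has 99.8% power with 43 children, and 21 children would give 90%. The 0.05 rule matches neither calculation.

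**2. How many primary scores?** (Section 6.5)

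| Group | Scores | Count |
| --- | --- | --- |
| Vocabulary | ROWPVT-4 | 1 |
| CELF-P3 language subtests | WS, SC, EV, FD, RS, BC, WC | 7 |
| CELF-P3 language indices | CLS, RLI, ELI-lan | 3 |
| Literacy | PRS, PA, ELI-lit | 3 |
| Total | | 14 |

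The two age versions of RLI are counted once. With five metrics each, the ceiling is 14 × 5 = 70 tests.

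**3. Chance of at least one false positive when no score truly differs**

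If independent, this is 1 − (1 − 0.05)^14 = 51.2%. For the 11 vocabulary and language scores alone it is 1 − 0.95^11 = 43.1%.

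The protocol gives no correlations, so a range was assumed. Simulation used 14 equally correlated normal test statistics, two-sided, with false positives counted in either direction:

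| Assumed pairwise correlation | 0.3 | 0.5 | 0.7 | 0.9 |
| --- | --- | --- | --- | --- |
| At least one P < .05 | 44% | 35% | 25% | 14% |

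If every metric were also tested, assumed correlations of 0.3 to 0.7 between scores and 0.90 to 0.95 between metrics of one score give about 36% to 68%.

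**4. What would a stricter level cost?**

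Bonferroni over 14 scores is 0.05/14 = 0.0036. The protocol's own 0.001 bounds the familywise error at 14 × 0.001 = 1.4%, whatever the correlation. Power per score for the stated 0.75 SD effect with 50 children is 98.4% at 0.0036 and 95.7% at 0.001.

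**The case against.** A reader might infer that a false positive is more likely than not, or that 70 tests will be run. The documents support neither reading. For one metric, only independence takes the figure past one half, and Section 6.5 describes the indices as composites of subtests on the same list, so independence is excluded. Section 17.1 says that the five metrics will be measured, not that each will be tested. Section 6.5 limits them to where they apply, and literacy scores start at age 4. Seventy is a ceiling.

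The aims in Section 2 include a pilot purpose: finding which outcomes respond most. Measuring many scores serves that aim. This softens the point but does not remove it, because the same section also states a central hypothesis that the intervention improves outcomes.

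A multiplicity method may stand in a statistical analysis plan that is not shown, and its absence from the protocol is not held against the trial. The point rests on what the protocol itself fixes: a P < .05 rule, a primary label on every score, and two other levels that disagree with the rule. The P < .05 sentence does read like a generic closing line, and nothing says that one significant score out of 14 would confirm the hypothesis. But nothing says what would, and it is the only decision rule given.

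Sizing at a stricter level than the one used for testing does not harm power; it leaves room to correct. That part of the defence stands and makes the remedy cheap.

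**Conclusion.** The point holds. The protocol contradicts itself on the significance level and on the status of literacy, and its stated rule, applied to the outcomes it calls primary, substantially inflates the false-positive rate. For 14 scores in one metric the familywise error is about 14% to 44% at assumed pairwise correlations of 0.9 to 0.3. The 51% figure is the independence limit only. Even the lowest value is nearly three times 5%. These sizes rest on assumed equal correlations and on all 14 scores being tested in a single metric; the contradictions between sections rest on no assumption.

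**What to change.** Before analysis, name one primary vocabulary or language score in one metric, tested at two-sided 0.05. Make all other scores, including all literacy scores, secondary, either Holm-adjusted or labelled exploratory. Treat the other metrics as descriptive. If the CELF-P3 Core Language Score is chosen, note that its standard score is also used in an exclusion criterion (Section 10).

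Alternatively, if all 14 scores stay primary, correct the Study Summary on literacy and replace P < .05 with an adjusted level: Holm or Bonferroni starting at 0.0036, or the protocol's own 0.001, which is stricter than 14 scores need. Power will be lower for literacy scores, which only children aged 4 and over can provide.

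In either case, state the one level in both Section 12.1 and Section 17.1. Remove the two-group calculation at 0.010, which does not fit the design in Section 6.1, where every child passes through the same two periods in the same order. Restate the power of the planned 50 children for the chosen score, metric and level. The present 0.75 and SD 1.0 are given for raw scores and need their own basis if another metric is chosen.

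The cost is a protocol amendment and a rewritten power statement, with no new data. If 0.05 is used, the need for 50 children must be justified afresh, since 21 would give 90% power for the stated effect. Under the single-primary option, most scores can no longer be claimed as primary successes.

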# Provisions to Monitor the Data to Ensure the Safety of Subjects*

This section is required when research involves more than Minimal Risk to subjects.

N/A – no more than Minimal Risk to subjects

# Provisions to Protect the Privacy Interests of Subjects

19.1 Describe the steps that will be taken to protect subjects’ privacy interests. “Privacy interest” refers to a person’s desire to place limits on whom they interact or whom they provide personal information.

Privacy and security will be maintained by minimizing the amount of identifiable data as much as possible. Only certified research personnel will be given access to identifiable participant information. All necessary identifiers will be used only to identify the relevant source documents. At the conclusion of data collection, a unique identifier will be assigned to each participant and the identifiers will be deleted from the primary dataset and stored in a separate list. A list linking the assigned code number to the individual subject will be maintained separately from the other research data.

19.2 Describe what steps you will take to make the subjects feel at ease with the research situation in terms of the questions being asked and the procedures being performed. “At ease” does not refer to physical discomfort, but the sense of intrusiveness a subject might experience in response to questions, examinations, and procedures.

No attempt to contact participants will be made beyond the contact in the study period.

Information will not be shared with anyone other than study personnel, or used for any other purpose other than the IRB approved purposes.

This information about privacy is provided to the families as part of the study and consent form.

Questionnaires filled by the participants are voluntary.

The participants will only potentially interact with a PI directly during the recruitment and informed consent process.

The PI may be familiar with some families and SLPs from their time in the clinic. Recruitment and consent activities will be conducted by trained Clinical Research Coordinators.

19.3 Indicate how the research team is permitted to access any sources of information about the subjects.

Study staff will use electronic medical records, a NCH secured shared drive, and REDCap to access confidential patient information. These systems will require NCH login. Access to these systems will be done only on NCH computers, and by study personnel.

Only trained and approved research personnel will be given access to identifiable participant information, including audio and visual recordings of participants. After completion of data collection and input into the limited data set, their charts will not be accessed for further data collection.

# Compensation for Research-Related Injury

**N/A** – no more than Minimal Risk to subjects

# Economic Burden to Subjects

21.1 Describe any costs that subjects may be responsible for because of participation in the research.

Participants are not expected to incur additional costs as a results of this study.

Economic risks are not expected to be excessive, given that interventions will take place during standard clinical care visits. No additional parking or transportation needs are expected.

Time spent learning and troubleshooting the software could occur. We will provide contact information to the Research Information Solutions and Innovation (RISI) at The Research Institute at Nationwide Children's Hospital, who is budgeted to provide ongoing support for this purpose.

Families will be provided study iPads and chargers.

No Wifi or internet is needed for use of the HMR app.

# Consent Process

22.1 Indicate whether you will you be obtaining consent, and if so describe:

**Child and Parent/Caregiver Participants:**

We will follow SOP: Written Documentation of Consent (HRP-091).

Potential subjects will be approached at a NCH site or via phone or email after identification and referral to study staff. Study personnel (not the PI) will discuss the study and review the consent form (in person, virtually, or over the phone) with the legal guardian or legally authorized representative. Please refer to the attached document: **Informed Consent** **Form.**

The written form and study information will inform potential participants about the details of the study and written in plain language at a level that reflects the reading ability of potential participants. The informed consent document will be reviewed and signed electronically, via REDCap. A copy will be emailed to the participant. The informed consent process may take place at NCH, virtually through a NCH-approved videoconferencing platform or via phone. A copy of **Informed Consent** **Form** will be provided to families as part of their study packet. Information about the study and researchers, including contact information, will be provided in case the family wishes to review documents on their own time and pace and notify the study staff of participation.

This study does not adversely affect the rights and welfare of subjects, and does not involve more than minimal risk.

If at any of the therapy visits, parents indicate they wish to withdraw from the study or consent, they may do so without retaliation.

No assent will be obtained from the children in this study, as all children will be under age 7 during the study period.

**Treating SLP Participants:**

The study team will contact treating SLPs who work with eligible children and invite them to participate in the study. Beyond standard of care, treating SLPs will be asked to complete 2 electronic surveys via REDCap for each child participant with whom they work.

We request a waiver of written documentation of informed consent. We qualify because:

- The research is not FDA-regulated.
- The research does not involve non-viable neonates.
- Participation involves completing online surveys the research involves no more than minimal risk.
- The research could not be carried out without using identifiable private information because we will need to obtain contact information to invite participants to participate.
- The waiver will not adversely affect the rights and welfare of participants because study staff will discuss the purpose of the study, how we will protect information, that the study is voluntary and will not impact their care or employment at NCH, and the participant’s right to withdraw at any time before sending the surveys to the participant. Treating Speech and Language Therapists will be provided with study information in oral (scripted) and written formats.
- Whenever appropriate, the subjects will be provided with additional pertinent information after participation. – NA, participants will complete a series of questionnaires and responses will be analyzed for the cohort, rather than individual participants. Therefore, there is no information to share with participants after participation.
- Waiver of consent for the storage, maintenance, or secondary research use of the identifiable private information or identifiable biospecimens cannot be granted for those who refused to provide broad consent. – NA, this study does not involve broad consent.

